## Discussion

Preparatory information benefits patients; de Freitas stated that online games are ‘applications using the characteristics of video and computer games to create engaging and immersive learning experiences for delivering specified learning goals, outcomes and experiences’ [29].

This study will be the first to test whether an interactive online GA-coping cartoon with an embedded video helps families to better, and more conveniently, prepare a child for surgery. We intend to focus on child dental patients because this is the most common group referred for general anaesthesia in the UK, yet it has the least ‘user friendly’ care pathway, it avoids sample variation in respect to anaesthetic method and surgery type, and is the service that will benefit most by reduction in family and staff stress and by resultant increase in throughput. However, in future, package access can be easily expanded UK-wide and the information gained used to develop further resources for children and adults who require other medical procedures such as blood tests.

We have based the sample size calculation on the blinded observer’s Visual Analogue Scale score at the actual moment of anaesthetic induction (A-VAS). Not only was this measure used in the Phase II RCT but it is also well validated for this purpose [16]. Moreover, the blinded researcher used the pilot study to train and calibrate this measure to avoid ‘ceiling’ effects and ensure reproducibility and reliability in the Phase III trial.

We also plan to use a 10 cm VAS (S-VAS) to measure family satisfaction with the preparatory information they received and with the service overall as they leave the hospital ward. The original plan was to use the TEI at this time, however, the pilot study showed that the families were tired and wanted to get back home at discharge time and were not keen to fully engage in a scoring measure that took longer and further delayed their departure. Therefore, we will use a simpler measure at time of discharge and score the TEI only at the telephone follow-up capture. Regarding the validity of these satisfaction measures, the use of a 10 cm VAS is superior to a Lickert scale when used as a single measure of patient satisfaction. It has also been validated for usage in this way and in a similar postoperative time period in adults undergoing arthroscopy [30]. We plan to ask the parents to report on the family satisfaction with the preparatory information that they received as well as the overall treatment experience using this 10 cm VAS (S-VAS). The TEI is a well-validated measure and has been slightly modified for the proposed study to clarify that it is scoring satisfaction with the preparatory information that was provided as well as the overall satisfaction with the service that the families rather than the dental treatment alone. The original author and validator of the TEI is one of the research team (TN) [21].

The removal of the ward discharge TEI capture point so that the only recording will be during a follow-up telephone call will mean that this measure will be collected by the unblinded researcher. However, given that the families are being asked specifically for their views about their allocated intervention, it would have been impossible to ensure continued researcher blinding in any case. Moreover, the TEI is a self-report measure. Nevertheless, this will have to be taken into account in the interpretation of the Phase III RCT results.

The FIS is well-validated for use, especially in dental settings. It is easy for a child to score this with the support of their parent or carer. It is a sheet of paper with symbols of faces [21]. It is the unblinded researcher who will have to collect this measure from the child on the ward since the child may be using the intervention or discussing it at that time point. Therefore, the researchers are aware that results obtained using this measure must be treated with caution. Indeed, the anxiety, psychological, and demographic data at the time of recruitment, family information such as maternal education and reported toothache on the day of the GA visit, as well as details of the anaesthesia, surgery and recovery, and analgesia will be used to report both equivalence between the groups and explain the patient journey so that the key results can be interpreted in context.

In paediatric dental anxiety studies it has been recommended that multiple measures are used; the researchers have adopted this principal for use in the Phase III RCT [31]. As such, we plan to use child and parent reporting as well as direct observation to record responses to the intervention. There are three key time points: on the ward before the anaesthesia, at the time of the anaesthetic induction, and then later at home. If this was a drug trial it would be easy to keep the data collection on the ward blind throughout, but since this is a computer intervention and the laptop computer will be open on the child’s bed (albeit with the curtains closed), the likelihood of unblinding is high. It is partly for this reason that such a comprehensive pilot study was needed.

Furthermore, ideally, the anaesthetists should be allowed to talk about the intervention with the child at the time of induction as it will help with the patient-doctor communication and engagement. Thus it might help with the anaesthetic induction and give a score in favour of the intervention. However, the researchers believe that blind data collection at this point is vital and so the hospital staff have been asked not to unblind RA.

The researchers have anticipated that data captured at the telephone follow-ups might be influenced by the Hawthorne effect since the families will already have met the researcher (CH) twice - once at recruitment and again on the ward [19]. CH is a trained researcher and is aware of this and of potential bias and will seek to minimise this. The pilot study helped to develop the script for the telephone dialogue so that the questioning of the families was kept as standard as possible for each telephone interview. Indeed, the principal investigator (MTH) in a previous RCT in this patient group noted that the personal engagement through frequent contact with study researchers might have had an adverse influence on the study outcome [28]. It is for this reason that the blinded researcher (RA) will not be introduced to the families and will collect mainly observational data.

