### Intervention

The intervention is an online GA-coping computer game. It is approximately 10 screens in length and takes about 15 minutes to play. It has a cartoon family, embedded video and contains preparatory information, role modelling, fasting instructions, and oral health messages and is specific to the dental surgery topic.

At the time of recruitment, each participant will be given the intervention pack as appropriate for their group allocation and advised to use it at home one week prior to the GA dental visit. In addition, both the study group and the hand-washing control group will be prompted once via email to use their online game at home. The reason for this prompt is to overcome the problem of a greater than two-week time lag between recruitment and GA dental visit due to service events (for example, if child is rescheduled due to having a cold). This type of child-coping intervention aimed at 5 to 7-year-old children is ideally used a week before the hospital visit to enable children of this age to assimilate the information.

All participants will be invited to use their intervention on the ward of the Day Surgery Unit at the time of the GA dental visit. All participants, irrespective of group, will be asked if they used their intervention at home. The researchers will be able to automatically verify usage of the GA-coping game since each will have a unique username. The website will also automatically monitor how often, how long and how far the participating families progress through the game.

The themes of the control interventions were selected for relevance; the colouring book was about healthy food choices and the computer game was about personal hygiene and hand-washing. The control group computer game was further matched to the test intervention on specific characteristics such as length of time taken to play, and has a similar combination of cartoon and human features as the intervention. The interventions have been well matched and thought through by the child psychologist on the research team (CL) and all have some dental and hospital relevance, but only the intervention group has preparatory information specific to both general anaesthesia and surgical tooth extraction.

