### Measures

The primary outcome measures are: (1) child cooperation and distress during the GA dental visit, on the ward before the procedure using the m-YPAS (time 1) (non-blinded researcher/observer reported) and the FIS child-reported to unblinded researcher [18,19]; (2) behaviour at anaesthetic induction by A-VAS score [16] and m-YPAS (time 2), reported by blinded researcher; (3) physical and psychological morbidity postoperatively using the Rutter Scale, Morbidity Checklist, and the Post Hospital Behaviour Questionnaire (unblinded-researcher recorded), parentally reported; (4) parent and child satisfaction using a 10 cm VAS (S-VAS) at the time of discharge from the Day Surgery Unit (parentally reported to the blinded observer) and the Treatment Evaluation Inventory at the 48 hour telephone call (parentally reported to the unblinded researcher); (5) service throughput will be measured using the duration of time in the induction room, duration of time in the recovery room, and duration of time on the ward before discharge (blinded-researcher recorded).

The secondary outcome measures are: the internet package usage by questioning about ease of access, acceptability, satisfaction- by parental reporting to the unblinded researcher at time of delivery of the allocated interventions, on the ward, and automatic recording via the internet.

The measures are detailed further:

At the time of recruitment the Rutter scale will test psychological well-being and status; this is a parental reporting tool but the unblinded researcher will be on hand to assist the parent with the questions if they have difficulty with literacy [23]. The child self-report of dental anxiety using MCDAs [20] supported by the Facial Image Scale (FIS) to aid comprehension [21], will be scored by the child themselves but supported by the unblinded researcher and the parent.

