At the time of the GA treatment visit on the DSU ward before being taken into the induction room all child participants will complete the FIS (FIS-ward) to self-report situational anxiety and the Bieri Scale to record pain (toothache) [26] and will be asked about their usage of the intervention. These will be recorded by the unblinded researcher since these families might be using their allocated intervention at this time. The child’s behaviour will be observed by the blinded observer and scored using the modified Yale Preoperative Anxiety Scale (m-YPAS-time 1) approximately 10 minutes before they are due to leave the ward and be taken into the anaesthetic induction room.

The behaviour at anaesthetic induction will be video recorded and the observed behaviour (acceptance of anaesthetic induction via inhalation) scored by the blinded researcher using m-YPAS(-time 2) and a 10 cm Visual Analogue Scale (A-VAS) rounded to the nearest to 0.5; the video recordings will enable future intra-rater reliability and reproducibility testing on the A-VAS [13,17,18].

During the surgical procedure the blinded observer will record the number of teeth extracted, the dose of local anaesthetic administered (routinely given to aid haemostasis), and the dose, preparation and route of analgesics administered (usually paracetamol or NSAIDs rather than opioids).

Service throughput will be reported in respect to the duration of time in the anaesthetic induction room, the duration of time in the recovery room, and the duration of time on the ward prior to discharge. These times are routinely recorded on the computer system at King’s College Hospital by the DSU staff for use in the generation of theatre utilisation data; the data will be recorded and accuracy of the recorded times will be verified by the blinded observer.

In the recovery room, children’s observed behaviour will be scored using a 10 cm Visual Analogue Scale, to differentiate this from the other visual analogue scales used in the study this will be termed R-VAS and will be scored by the blinded researcher.

At the time of discharge, parents will be asked to rate their satisfaction with the preparatory information by the blinded researcher using a series of questions scored using a further 10 cm VAS (S-VAS).

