### Statistical analysis

Intention-to-treat methodology will be employed. Descriptive statistical summaries for all explanatory variables at baseline will be provided, overall and by study group. Analysis of Variance and Chi-square tests will be used to highlight any significant imbalance between groups. The GA-coping game’s effect on the key primary outcome measures and the 10 cm VAS and the m-YPAS for child behaviour at anaesthetic induction, will be compared with the two controls and will be modelled using linear or ordinal regressions as appropriate. Multivariate models will be fitted so that any confounding effect is assessed and adjusted for if necessary.

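### Data recorded after exposure to the game (ward toothache, anaesthesia, recovery, analgesia) are named as evidence of group equivalence, so an effect of the game could be read as imbalance

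*Protocol article*

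**What the plan says.** **Equivalence (Discussion).** One sentence gathers the recruitment data on anxiety, psychological status and demographics, "family information such as maternal education and reported toothache on the day of the GA visit", and then continues "as well as details of the anaesthesia, surgery and recovery, and analgesia will be used to report both equivalence between the groups". Its second stated purpose is to explain the patient journey so that the results can be read in context.

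**Timing of exposure (Intervention).** "At the time of recruitment, each participant will be given the intervention pack as appropriate for their group allocation", for use at home about a week before the visit. Then: "All participants will be invited to use their intervention on the ward of the Day Surgery Unit at the time of the GA dental visit".

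**Timing of the treatment-day items (Measures).** Toothache (Bieri scale) and the child's self-reported anxiety are taken on the ward: "These will be recorded by the unblinded researcher since these families might be using their allocated intervention at this time". Surgical details and analgesics are recorded during the operation, and recovery behaviour (R-VAS) in the recovery room.

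**Outcome status (Measures).** Primary outcome (5) reads "service throughput will be measured using the duration of time in the induction room, duration of time in the recovery room", followed by time on the ward before discharge.

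**Equivalence elsewhere.** The section on the blinded observer says that the psychological and dental-anxiety measures taken at recruitment serve to inform equivalence. The Statistical analysis section promises descriptive summaries of explanatory variables at baseline, with analysis of variance and chi-square tests for imbalance. It adds: "Multivariate models will be fitted so that any confounding effect is assessed and adjusted for if necessary".

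**The concern.** Equivalence between randomised groups is a statement about the groups before the intervention could act. A variable recorded afterwards mixes any chance imbalance with any effect of the intervention, and the two cannot be separated.

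The protocol itself gives reasons to expect such effects. Its Background says that preparation reduces distress and postoperative complications. The hand-washing game is included because computer use on the ward might distract the child, which makes some effect on self-reported toothache possible. The primary aim includes anaesthetic time and throughput. The section on the blinded observer counts details of the operative procedure, such as anaesthetic type, among the key outcome measures of the day.

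Two things are at stake. First, a real benefit in recovery or analgesia could be described as non-equivalence and used to discount the result. Second, because the adjustment rule names no limit on covariates, a variable flagged in this way might later be offered as a confounder. The documents support the first as a consequence of what they state, and the second only as a risk.

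**Working it through.** **1. Order of events** (Protocol article: Intervention, Measures, Participants)

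| Step | Item | Could allocation affect it? |
|---|---|---|
| Recruitment, about two weeks before | Age year, gender, MCDAs, Rutter, demographics | No |
| Home | Pack available to all, with an email prompt to both game groups | (exposure) |
| Ward | Laptop with a game for two groups; toothache recorded | Possible, though less likely than for recovery |
| Induction | A-VAS, m-YPAS time 2, induction-room time | Yes (primary outcomes) |
| Surgery | Teeth extracted, local anaesthetic, analgesics | Teeth extracted unlikely; analgesia possible |
| Recovery | Recovery-room time (primary outcome), R-VAS | Yes |
| One week | Parent age, education, household | Very unlikely, although collected late |

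The Discussion draws on both sides of the exposure line for equivalence. The other two sections point to recruitment or baseline data.

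**2. The plan's own sample size.** Inputs from Power calculation: difference 2 cm, SD 3.1, power 90%. Alpha is not stated; two-sided 0.05 is assumed.

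n = 2 × (1.960 + 1.282)² × 3.1² / 2² ≈ 50.5, so 51 per group; the t-test version gives 51.5, so 52. The stated 53 is within two children of this, and power at 53 is 0.913 by the normal approximation. The point does not dispute this figure, and the fix does not change it.

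**3. How often an effect would be flagged as imbalance.** Suppose randomisation is perfect and the game shifts a treatment-day variable by d SD in one of three arms. The one-way analysis of variance has noncentrality

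λ = n × [(2d/3)² + 2 × (d/3)²] = n × (2/3) × d²

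with 2 and 3n − 3 degrees of freedom. At n = 53 and d = 0.5, λ = 53 × 0.667 × 0.25 = 8.83. Against a 5% critical value of 3.05 on 2 and 156 degrees of freedom, the rejection probability is 0.754.

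| Assumed true effect (SD) | 53 per group | 70 per group |
|---|---|---|
| 0 (true baseline variable) | 0.05 | 0.05 |
| 0.2 | 0.17 | 0.21 |
| 0.3 | 0.33 | 0.43 |
| 0.5 | 0.75 | 0.87 |
| 0.645 (2/3.1, the planned A-VAS effect) | 0.94 | 0.98 |

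The effect sizes are assumptions, since the documents give none for recovery, analgesia or toothache. The table also assumes that the planned imbalance tests are applied to these items, which the Statistical analysis section does not say.

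**The case against.** The sentence stands in the Discussion, not in the analysis section, and it has two purposes. One could read it distributively: recruitment data serve equivalence, and peri-operative data serve the patient journey. The imbalance tests follow directly on a sentence about baseline variables and are naturally read with it. Comparing surgery and co-treatment across arms is also sensible, since number of teeth and local anaesthetic are set largely by clinical need and by staff who are meant to be blinded.

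Much of this stands. The descriptive purpose is legitimate, number of teeth extracted is unlikely to respond to the game, and the flagging rates above are conditional. The distributive reading, however, strains against a sentence that assigns both purposes to the whole list.

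Stronger readings are tempting, and the documents do not support them:

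- **That the plan will adjust these variables away and shrink the 2 cm A-VAS effect.** Nothing places toothache, anaesthesia, recovery or analgesia in a model, and a covariate list may properly sit in the analysis plan. Recovery and intra-operative analgesia also come after induction, so they cannot carry part of the effect on A-VAS. No size is put on this risk.
- **That an effect on recovery time would be reported only as imbalance.** Recovery-room duration remains a throughput outcome and would be reported as such. The Discussion speaks of recovery details without naming that duration, so the overlap is possible but not certain.

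**Conclusion.** The point holds in a limited form. The protocol article names data recorded after allocation and after offered exposure as evidence of equivalence, against the baseline or recruitment basis given in two other sections. For variables that the game can change, this invites a genuine effect to be read as failed balance. Under an assumed 0.5 SD effect, and if the imbalance tests were used on such a variable, that would happen in about 75% of trials at 53 per group, against 5% for a true baseline variable. With smaller assumed effects of 0.2 to 0.3 SD the figure is 17% to 33%.

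The open adjustment rule makes misuse of these variables as covariates possible, but it is not a stated plan. The sample size and the list of outcomes are unaffected. The passages should be reconciled, because the correction is cheap and the text as it stands supports a wrong interpretation.

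**What to change.** In the Discussion and in Statistical analysis:

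- Limit equivalence reporting and candidate covariates to variables that allocation cannot affect: age year, gender, MCDAs and Rutter at recruitment, demographics, and stable family characteristics such as parental education. The test is whether the game could change the variable, so late collection at one week does not exclude the last group.
- Report ward toothache, anaesthesia, surgery, recovery and analgesia by arm as process or outcome data. This keeps the patient-journey purpose.
- State that these treatment-day items are not covariates in the models that estimate the game's effect.
- The section on the blinded observer reserves the recruitment measures for equivalence alone. Align that sentence if MCDAs and Rutter are to be candidate covariates.

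The cost is a change of wording, with no new data and no change in sample size. Recruitment has closed, but the article says that allocation stays concealed until the analysis is concluded, so the rule can still be fixed without knowledge of results by arm if that analysis has not been completed.

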## Trial status

The trial closed on 4^th^ June 2014, 185 participants were recruited, the attrition rate was less than anticipated and so the target sample number of 53 was met in each group more readily than anticipated.

## Abbreviations

A-VAS: Anaesthetic induction 10 cm VAS; DSU: Day Surgery Unit; FIS-ward: Facial Image Scale used by child to self-report anxiety on the ward; FIS-48: Facial Image Scale used by child to self-report anxiety at the 48 hour follow-up call; FIS-7: Facial Image Scale used by child to self-report anxiety at the 1 week follow-up call; GA: General anaesthesia; KCH: King’s College Hospital NHS Foundation Trust; MC: Morbidity Checklist used here to record both 48 hr and 1 week morbidity; MCDAs: Modified Child Dental Anxiety score; m-YPAS: modified Yale Preoperative Anxiety Scale; PHBQ: Post Hospital Behaviour Questionnaire used here to record 48 hr and 1 week morbidity; satis-VAS: 10 cm VAS at discharge to measure family satisfaction with the preparatory information; TEI: Treatment Evaluation Inventory used to rate the overall family view of the service they received and their satisfaction with the preparatory information.
